### Data entry, missing data, loss to follow-up and withdrawal

All data will be analysed on an intention to treat basis. Data entry, coding, security and storage are planned and provided within Castor EDC, including data quality checks such as checks on double data entry, range checks for data values, etc. [19].

Missing data will be imputed with multiple imputation if assumed to be missing at random. Patients lost to follow-up or dropping out will not be replaced for it might indicate problems in feasibility.

Subjects can leave the study at any time for any reason if they wish to do so without any consequences. The reason will be documented on the case report form. Patients who have withdrawn themselves from the study will receive treatment and follow-up according to national protocol.

### Sample size calculation, data monitoring and premature termination of the study

We will include 15 patients in each arm for this phase II study. There will be no formal data-safety monitoring board due to the relatively small number of patients (*n* = 15) in the intervention arm. However, due to the nature of this intervention and possible risk related to the intervention, we have installed an independent expert to ensure the safety and ethics. After each serious adverse event, which may in any way be related to the para-aortic lymphadenectomy, all inclusions and planned interventions at all centres will be stopped immediately. All principle investigators will converge and decide whether it is ethical to resume inclusion after the serious adverse event has abated or until a stable situation has been reached. All meetings and decisions will be documented. Each conclusion will be submitted to the independent expert for an independent assessment on safety and ethics. The trial will only resume after both the principle investigators and independent expert agree that safety and ethical criteria are being met. An independent monitor will check all centres on informed consent, adherence to the in- and exclusion criteria, reporting of all adverse events and full source document verification. The monitor will audit after the first three included patients and then yearly or after every 10 included patients.

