### Radiotherapy and adjuvant chemotherapy

All patients will be treated with both external beam radiotherapy (EBRT) and brachytherapy. The choice for applying extended field radiotherapy will be based on surgical staging or PET-CT, according to the results of the study arm. Concomitant chemotherapy will consist of 5 cycles of weekly cisplatin (40 mg/m2), coinciding the first dose of chemotherapy with the first dose of radiotherapy.

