### Secondary study parameters and analysis

Although this is a phase 2 trial, we will also register secondary outcome parameters such as (progression-free) survival and quality of life as they are also aspects of safety. The incidence of advanced stage cervical cancer is quite low in the Netherlands. Including these secondary parameters will make it possible to enter these patients into a subsequent phase 3 trial, if the current PALDISC study shows that such a phase 3 study is indeed necessary. Decision on the necessity of a phase 3 trial will depend on whether surgical staging of PALN in advanced stage cervical cancer is deemed safe, feasible and necessary in comparison with the performance of current PET-CT imaging.

The proportion of changed initial treatment plans and diameter of metastases will be documented and presented. Data on sensitivity, specificity and negative and positive predictive values of MRI, PET-CT and surgical staging will be documented in 2 × 2 tables; estimates will be provided with 95% CI.

Time to treatment will be measured in days from the day of randomization until start of chemo radiation. Difference in treatment delay between the arms, due to surgical intervention and histological analyses, will be presented using a Kaplan-Meier curve with the corresponding medians and 95% CI. Rate differences and 95% CI for mortality and morbidity during follow-up will be calculated and presented in a table.

The analysis of progression-free survival and overall survival will be based on and presented in a Kaplan-Meier curve with corresponding hazard ratio and 95% CI. Means and range in reported quality of life will be reported using the Dutch versions of the European Organisation for Research and Treatment of Cancer (EORTC) Core Questionnaire, the QLQ-C30 version 3.0 and the supplemental cervical cancer-specific module, the QLQ-CX24 [24, 25]. The difference in quality of life between the arms will be presented as a mean difference with 95% CI.

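### Days lost to a trial-wide halt after another patient's SAE would be reported as treatment delay caused by surgery and histology

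*Protocol article*

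**What the plan says.** All references are to the protocol article.

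- **Trigger and scope of the halt** (Sample size calculation, data monitoring and premature termination of the study): "After each serious adverse event, which may in any way be related to the para-aortic lymphadenectomy", the instruction is that "all inclusions and planned interventions at all centres will be stopped immediately". No severity or count threshold is stated.
- **Length and restart** (same section): the investigators meet and "decide whether it is ethical to resume inclusion after the serious adverse event has abated or until a stable situation has been reached". Then: "The trial will only resume after both the principle investigators and independent expert agree that safety and ethical criteria are being met". No maximum is given. The decision described concerns new inclusions; women already randomised to surgery are not mentioned.
- **Delay clock** (Secondary study parameters and analysis): "Time to treatment will be measured in days from the day of randomization until start of chemo radiation".
- **Attribution** (same section): "Difference in treatment delay between the arms, due to surgical intervention and histological analyses, will be presented using a Kaplan-Meier curve", with medians and 95% CIs.
- **Standing of the outcome**: the abstract lists treatment delay due to surgical staging among the primary safety and feasibility outcomes, summarised by means. The body of the article treats it as secondary.
- **Field decision** (Radiotherapy and adjuvant chemotherapy): "The choice for applying extended field radiotherapy will be based on surgical staging or PET-CT, according to the results of the study arm".
- **Analysis set** (Data entry, missing data, loss to follow-up and withdrawal): intention to treat.

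**The concern.** Each rule is reasonable alone, but together they mislabel some of the delay. If the patient with the SAE starts chemoradiation late, that is a consequence of her operation. If a second patient's operation is postponed because of that event, her extra days come from the trial's safety procedure: the event settling, the investigators meeting and the expert agreeing. They are neither operating time nor histology time. The clock nevertheless counts them, intention to treat keeps them in, and the text assigns the whole between-arm difference to surgery and histology.

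The article does not define planned interventions. Since the trigger is a lymphadenectomy SAE, the operations are the natural reading. On that reading controls have nothing pending to suspend, and the halt days go in one direction, against surgery.

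Delay contributes to the judgement whether surgical staging is safe and feasible, and so to the decision on a phase 3 trial. The article also does not say how a woman already allocated to surgery proceeds while operations are suspended and her field decision is tied to the surgical result.

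**Working it through.** **Plan's own figures.** The article gives 15 per arm (15 + 15 = 30, as in the abstract). It states no SAE rate, halt length, wait for surgery or expected delay, so there is no delay figure to reproduce. Everything below except the 15 and the observed accrual is an assumption, shown over a range.

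**Step 1: chance of at least one halt.** With related-SAE probability p per operation, P = 1 − (1 − p)^15 and the expected number of halts is 15p.

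| Assumed p | P(at least one halt) | Expected halts |
|---|---|---|
| 5% | 1 − 0.95^15 = 54% | 0.75 |
| 10% | 1 − 0.90^15 = 79% | 1.5 |
| 20% | 1 − 0.80^15 = 96% | 3.0 |
| 30% | 1 − 0.70^15 = 99.5% | 4.5 |

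This is the chance that a halt occurs, not that a patient is caught in one.

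**Step 2: surgical-arm patients caught.** Inclusion stops too, so only women already randomised and awaiting surgery are exposed. Expected number caught = arm accrual per day × wait from randomisation to surgery × expected halts, for waits of 7–21 days and p of 10–30%.

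- Arm filled in 24 months: lowest 15/730 × 7 × 1.5 = 0.2; highest 15/730 × 21 × 4.5 = 1.9.
- Arm filled in 12 months: lowest 15/365 × 7 × 1.5 = 0.4; highest 15/365 × 21 × 4.5 = 3.9.
- Observed pace (Trial status: five patients from July 2015 to October 2017, so about 2.5 per arm in some 822 days), were 15 operations reached: highest 2.5/822 × 21 × 4.5 = 0.3.

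**Step 3: shift in the reported delay.** With k of 15 patients held D days, the mean moves by kD/15. The median shift was simulated with an assumed lognormal delay (median 28 days, log-SD 0.25).

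| k caught | D = 14: mean / median shift (days) | D = 28: mean / median shift (days) |
|---|---|---|
| 1 | 14/15 = 0.9 / 0.6 | 28/15 = 1.9 / 0.6 |
| 2 | 28/15 = 1.9 / 1.3 | 56/15 = 3.7 / 1.4 |
| 4 | 56/15 = 3.7 / 3.2 | 112/15 = 7.5 / 3.5 |

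The mean named in the abstract is more exposed than the Kaplan-Meier median in the body. A patient who is held has the full D days added to her own time to treatment.

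**The case against.** **The effect is small and the study descriptive.** There is no formal test and no delay threshold, the inclusion stop limits who can be caught, and the median absorbs much of what remains. This stands, and it limits the size of the point. It does not make the attribution right, and faster accrual would catch more women. The trial is cancelled, but the authors publish partly to interest other centres in such a trial, so the rules may be reused.

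**Halts already leave a trace.** Meetings and decisions are to be documented, so dates could be recovered later. That is true and makes the fix cheap, but nothing in the article links those records to the delay analysis.

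**One-sidedness is not certain.** This stands: it depends on what planned interventions means, so the point is conditional there.

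**Stronger readings the article does not support.** A reader might infer that a surgical-arm patient caught in a halt must wait untreated or withdraw. No section says so. The intervention arm receives surgical staging on top of regular treatment and PET-CT. Only the choice of extended field is tied to the arm, not the start of chemoradiation. The sections on control care and on withdrawn patients do not reserve those routes to them. The full protocol, which is not shown, may cover the case.

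A reader might also infer that drop-out during a halt is counted as infeasibility. The text is "Patients lost to follow-up or dropping out will not be replaced for it might indicate problems in feasibility", which explains why drop-outs are not replaced and sets no counting rule. Reasons for withdrawal are recorded, and the stated feasibility measure, included among eligible, does not change when a randomised patient leaves. Nor is there a case for disregarding halt-related drop-out: it follows an event possibly caused by the procedure and may be informative.

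**Conclusion.** The point holds as a misattribution. Under the stated rules, halt days of surgical-arm patients awaiting their operation are counted in time to treatment and reported as due to surgery and histology. That the bias falls on one arm depends on planned interventions meaning the operations.

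The size is probably modest: with 24-month accrual about 0.2–1.9 of 15 patients caught, and with one or two caught for 14–28 days a shift of 0.9–3.7 days in the mean and about 0.6–1.4 days in the median. These figures rest on assumed SAE rates, waits, accrual, halt lengths and, for the median, an assumed delay distribution. The 54–96% chance of a halt at SAE rates of 5–20% must not be read as the chance that anyone is affected.

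How already-allocated patients proceed during a halt is unclear in the article. That is a matter for clarification, not evidence that patients are left without treatment.

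**What to change.** 1. Record the start and end date of each halt, and which surgical-arm patients were randomised and awaiting surgery at that time.
2. Report time to treatment by arm with all days counted, as the intention-to-treat result, and again with halt days shown separately or removed.
3. Amend the attribution in Secondary study parameters and analysis so that the between-arm difference is not ascribed wholly to surgery and histology when halts have occurred. State what planned interventions covers.
4. Reconcile Control group, Radiotherapy and adjuvant chemotherapy, the withdrawal text and the halt rule, so that it is clear how a patient already allocated to surgery when a halt begins proceeds to chemoradiation within the trial. The route is for the investigators and the independent expert to decide.

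Cost: a short clarification, two dates on the CRF with a note of who was waiting, and one extra descriptive line. Sample size and the main analysis do not change.

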### Recruitment and consent

The rationale, design and aims of the study will be explained to each patient along with the specific information on the respective treatment arms. The principles of registration and the follow-up procedure will be explained, and patients will receive written patient information and will have ample opportunity to ask questions. Written informed consent of the patient is required before inclusion and will be obtained by the clinician.

### Risk assessment

Due to experience with the procedure and known incidence and severity of complications, the risk associated with the intervention is estimated to be moderate. Para-aortic lymphadenectomy is new in cervical cancer but a common procedure for gynaecological oncologists in ovarian and endometrial cancer.

### Ethical considerations

The protocol has been reviewed and approved by the Radboud Medical-Ethical Committee (METC) on the 4th of September 2014 with reference number: 2014/240 and registration number: NL49310.091.14, as well as approved by the Radboudumc Board of Directors on 21st of October 2014 with reference number: RvBI4.5 L737. (supplements in Dutch) The study is being conducted in full conformance with the ethical principles of the Declaration of Helsinki Seoul, 2008, the WMO, the Dutch guidelines ‘richtlijn toetsingsprocedure multicenter-onderzoek’ (active as of 1 January 2001) and ‘good clinical practice’.

### Public disclosure, availability of data and materials and publication policy

Within 1 year after the end of the study, a final study report with the results of the study will be submitted, including any publications/abstracts of the study to the accredited ethical committee. Publications and abstracts will be published according to policy of the Central Committee on Research Involving Human Subjects.

The final trial results will be submitted to a peer-reviewed scientific journal for publishing irrespective of the nature of the results.

## Discussion

The PALDISC trial will assess safety and feasibility of surgical staging in patients with locally advanced cervical cancer in the Netherlands. It will provide insight in diagnostic accuracy of the PET-CT and detection rate of missed (micro)metastases due to surgical staging.

So far, all available evidence regarding the validity and diagnostic accuracy of PET-CT in detecting PALN metastases in locally advanced cervical cancer is based on a study with 16 patients only [10]. This leads to a high uncertainty regarding both sensitivity and specificity, which is represented by the large confidence intervals. As a result, patients may have a high chance on false negative and/or false positive PET-CT results, leading to subsequent under- and overtreatment, respectively. Undertreatment may lead to a deterioration of overall and progression-free survival, while overtreatment may lead to unnecessary radiation. Both have detrimental effects on the quality of life of patients as well as hospital and health care expenses.

To compare the effectiveness and diagnostic accuracy of a PET-CT with surgical staging, a phase 3 randomised controlled trial is the most warranted design. However, as para-aortic lymphadenectomy is not standard of care for cervical cancer patients in the Netherlands, we feel the need to first assess its safety and feasibility.

A major strength of our study is that safety and feasibility of the para-aortic lymphadenectomy is assessed on both subjective (quality of life) and objective (time of treatment delay, blood loss, adverse events, etc.) outcome measures. In addition, data on both sensitivity and specificity should also be considered. Although this study only includes 15 patients, it is almost a doubling of the currently available number of patients in whom PET-CT was compared to gold standard histology (*n* = 16) [10]. Furthermore, these outcomes can be compared to current standard of care while controlling for confounders and selection bias due to the randomization. These strengths will provide vital information for a group of experts in order to make the final decision whether or not a phase 3 trial is deemed safe and necessary.

As for most surgical trials, blinding is not possible. To preclude bias due to this lack of blinding, we have chosen objective outcomes on safety and feasibility as the primary outcome for this trial and the subjective quality of life as a secondary outcome. Combining these results will provide insight in the safety and feasibility of para-aortic lymphadenectomy in advanced stage cervical cancer.

## Trial status

The PALDISC trial is currently cancelled, and further inclusion is on hold due to a too low inclusion rate. Recruitment began in July 2015 and a total of five patients were enrolled by October 2017. This low inclusion rate which has led to the cancellation of the study is mainly due to the fact that the incidence of advanced stage cervical cancer is low in the Netherlands and there was only one actively participating centre. With the publication of this protocol, we do hope to spark the interest of other centres for such a trial. In addition, we would like to open a scientific discussion on the diagnostic accuracy of the PET-CT as there is currently no study that compares PET-CT positive results to gold-standard histology analyses. The specificity of 83% (95% CI; 52–98%) based on only 16 patients implies that possibly 17% of all patients have false positive PET-CT results without PALN metastases. This may lead to misinformed treatment decisions including ‘unnecessary’ extended field radiotherapy with associated comorbidities. As such, more evidence on both the sensitivity and specificity of the PET-CT is warranted.

## Abbreviations

AE: Adverse event
CI: Confidence interval
CT: Computed tomography
EBRT: External beam radiotherapy
EORTC: European Organisation for Research and Treatment of Cancer
FIGO: International Federation of Gynaecology and Obstetrics
METC: Medical-Ethical Committee
MRI: Magnetic resonance imaging
PALN: Para-aortic lymph node
PET: Positron emission tomography
QLQ-C30: Quality of Life Core Questionnaire
QLQ-CX24: Quality of Life Questionnaire cervical cancer specific
WBC: White blood cell
WHO: World Health Organization
WMO: Medical Research Involving Human Subjects Act (in Dutch: Wet Medisch-wetenschappelijk Onderzoek met Mensen
